### Data Collection

Study nurses will enter data into the eCRF either directly or by transfer of an extract from the patient’s electronic registry file (Qualität in der Nephrologie [QiN]; English: Quality in Nephrology database). The registry will also alert the study nurse to events during follow-up such as hospitalization, death, and transfer out of the dialysis unit, which are reliably captured because they are needed for billing purposes.

The central data repository will be the eCRF. Source documents will be stored in each patient’s study file.

### Study Procedure

In principle, all KfH dialysis practices will be eligible to participate in this study. KfH practices can be considered representative of the German dialysis population since they are widely distributed throughout Germany and about 20%-25% of all hemodialysis patients are treated there. Site selection will depend on the willingness of the attending physicians to participate and key characteristics of the practice (eg, site location and number of patients). Criteria for site selection will be developed by QiN-group and DZIF-Köln. A number of suitable KfH dialysis practices will be allocated to each of the 12 DZIF CTU sites: Universitätsklinikum Bonn, Medizinische Klinik Borstel, Universitätsklinikum Eppendorf, Universitätsklinikum Gießen und Marburg, Standort Gießen, Medizinische Hochschule Hannover, Universitätsklinikum Heidelberg, Universitätsklinikum Köln (AöR), Universitätsklinikum Schleswig-Holstein/Campus Lübeck, Universitätsklinikum Gießen und Marburg, Standort Marburg, Klinikum der Universität München, Technische Universität München, and Universitätsklinikum Tübingen.

QiN-group will assist DZIF CTU personnel with site selection and internal KfH study participation formalities. DZIF CTU personnel will cooperate with the KfH physicians to assist in setting up subject prescreening and informed consent procedures. Informed consent will be obtained by treating physicians.

The sample size has been calculated to demonstrate a significantly lower all-cause community-acquired pneumonia (CAP) rate in newly vaccinated patients compared to patients vaccinated more than 2 years before enrollment.

The incidence of pneumonia in hemodialysis patients was reported as 29.0/100 patient-years (py) [14]. Data on the efficacy of pneumococcal vaccines for preventing pneumonia in hemodialysis patients is lacking. However, a recent meta-analysis demonstrated pneumococcal vaccination to result in a relative risk for pneumonia of 0.72 (95% CI 0.69-0.94) in an immunocompetent target population (ie, adults at risk or >65 years) [8].

In general, immunological studies in hemodialysis patients have been carried out with limited patient numbers and in mixed populations (CKD, hemodialysis, and renal transplant recipients) [9]. Most studies suggest good initial immunogenicity, but titers seem to significantly decline after 6 to 12 months in adult dialysis patients [10]. The limited number of studies with longer follow-up periods suggests a possible benefit of revaccination after 2 years [11,12].

For the purpose of this calculation, we assume protection from pneumonia in the first 2 years to be equal to the protection recently demonstrated in an adult immunocompetent target population (relative risk 0.72) and afterward return to baseline. Thus, expected rates of pneumonia are 29.0/100 py in patients vaccinated >2 years ago and 20.88/100 py in patients vaccinated <2 years ago, respectively. To demonstrate the superiority of a more recent vaccination in preventing pneumonia with α=.05 and (1–β)=0.80, we would thus require 2 groups of 442 patients each (884 patients overall). Furthermore, the rate of pneumonia is also likely to be greater in an underprotected population than seen in the overall hemodialysis population, which includes a relevant number of freshly vaccinated patients. Additionally, the possibility of an unbalanced distribution of recently vaccinated patients (in a ratio of up to 1:7) was considered. A first statistical analysis will be discussed in an interim study report after 18 months.

### Amendment After Interim Study Report

After an enrollment period of 18 months, which had been extended twice, 710 patients had been included in the study and had a fully documented vaccination status, 174 less than planned. 596 had been vaccinated less than 2 years ago, and 114 had been vaccinated 2 or more years before enrollment, respectively. This represents a ratio of 1:5, which was well within the range of an unbalanced patient distribution, which had been explored in the sample size calculation. Assuming that further recruitment would continue at this ratio and that risk reduction remained at 0.72, 792 patients were then considered sufficient if the observation period was extended to 2.5 years. These assumptions yielded a power (1–β) of 0.81 while keeping the type-I error at α=.05.

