Participating sites will screen all hemodialysis patients at their outpatient dialysis clinic for eligibility. Eligible patients will be approached and informed by their physicians. If a patient agrees to participate in the study and signs an informed consent form (ICF), basic data regarding vaccination history, underlying disease, and so on will be entered or imported electronically into the study eCRF. Pneumococcal antibody titers will be drawn at baseline and every 3 months. For newly vaccinated patients, baseline titers will be drawn 4 weeks after vaccination. Deutsches Zentrum für Infektionsforschung (DZIF; English: German Center for Infection Research) clinical trial units (CTUs) will coordinate titer assessment schedules and inform the participating physicians of upcoming blood samplings. The samples will be taken on dialysis days from an already inserted-intravascular catheter. DZIF CTUs will actively follow up on study patients for 2-5 years after enrollment. This follow-up will include validation of all hospitalizations and deaths documented in the electronic registry to assess whether the primary end point (all-cause pneumonia) occurred. During months 25-30, only the primary end point will be recorded (ie, no blood samples will be taken). Additionally, dialysis units will be contacted every 6 months to assess if pneumonia occurred that did not require hospitalization. Blood samples will be stored frozen at DZIF CTUs, and titers will be analyzed at the end of this study. All therapies and diagnostics, including vaccinations, will be administered solely as part of the clinical routine and as recommended by appropriate guidelines (eg, RKI Ständige Impfkommission [STIKO] recommendations). Thus, Arzneimittelgesetz (AMG) does not apply to this study, and participating physicians do not require Good Clinical Practice (GCP) certification.

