### Study Conduct and Statistical Analyses

The primary objective of this study is to compare pneumonia rates and outcomes between both groups. To achieve this, the raw number of events and raw rates of events per 100 patient years will be computed. For each group, the mean, median, SD, IQR, and minimum and maximum of demographical variables like age and sex will be computed. These observed variables will be used to build a Cox proportional hazard model. If applicable, this model will incorporate time-varying covariates and consider recurring events. To quantify the expected protective effect of a high titer level, multiple functional relationships will be explored, including but not limited to linear, quadratic, and step functions. Step functions will be created by dividing the titer levels into 10 mutually exclusive strata and estimating each risk individually. If possible, the largest difference between 2 neighboring strata will be identified as a threshold for an adequate titer level.

The secondary objectives of this study are to describe antibody titers as a function of time and factors influencing antibody kinetics. Descriptive statistics for titer levels at all intervals will be computed for absolute values as well as relative values (relative to the first observed or personal maximum). Levels for patients grouped by age, sex, and other variables of interest will be calculated. To allow a comparison, the mean, median, SD, IQR, and minimum and maximum titer levels will be calculated.

To identify which factors influence the absolute antibody titer level, multiple multivariate models will be built. In patients with available titers, risk factors for insufficient protection will be determined by multiple regression analyses of data including vaccination history and timing, medication exposure since last vaccination, history of underlying kidney disorder, dialysis, and demographic factors.

The titer levels will be assessed graphically by comparing boxplots of the titer levels at different time intervals. Concurrent titer levels will be tested for statistically significant differences by using a *t* test or a Mann-Whitney U test, whichever is applicable.

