### Conclusions

Current vaccination schedules recommend pneumococcal vaccination for CKD-5D patients every 6 years. However, this timing disregards findings of rapid titer decline in adult hemodialysis patients after 6 to 12 months. By comparing pneumonia rates between recently vaccinated patients and those who were vaccinated more than 2 years ago, we may estimate the duration of protection by antipneumococcal vaccination. In addition, antipneumococcal antibody titers in hemodialysis patients will be determined as a function of time since vaccination and provide further conclusions.

Through its conduct, this prospective study will increase physician adherence to current recommendations. Establishing a framework for the efficient evaluation of guideline recommendations through a combination of routine and study data will inform the evidence base for future guidelines.

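### The amended power of 0.81 holds the relative risk at 0.72 for 2.5 years, which contradicts the plan's own assumption that protection ends 2 years after vaccination

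*Protocol article*

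**What the plan says.** All references are to the protocol article.

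- *Study Procedure* sets the planning effect: "relative risk 0.72) and afterward return to baseline". The 0.72 is applied to the first 2 years after vaccination, giving 20.88 per 100 patient-years against 29.0 per 100 patient-years thereafter.
- The same section states the comparison to be powered as newly vaccinated patients "compared to patients vaccinated more than 2 years before enrollment", so the older group is anchored at enrollment.
- *Amendment After Interim Study Report* counts the groups on that basis: "596 had been vaccinated less than 2 years ago, and 114 had been vaccinated 2 or more years before enrollment". It treats this as 1:5, keeps the risk reduction at 0.72 and concludes that "792 patients were then considered sufficient if the observation period was extended to 2.5 years", with power 0.81 at α = .05.
- *Study Design* confirms that the primary end point is still recorded in months 25 to 30. It also says that all treatment, "including vaccinations, will be administered solely as part of the clinical routine", so revaccination during follow-up is possible.
- *Study Conduct and Statistical Analyses* compares both groups by raw rates per 100 patient-years and builds a Cox model. Of that model it says: "If applicable, this model will incorporate time-varying covariates and consider recurring events". Vaccination status is not named there as a time-varying term.
- *Conclusions* says of the comparison that "we may estimate the duration of protection by antipneumococcal vaccination".

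**The concern.** The amendment extended follow-up to recover power lost through lower recruitment and unequal groups. Extra follow-up adds power only if the two groups still differ in risk during it. Under the plan's own model, a patient vaccinated on the day of enrollment and not revaccinated has no protection left in months 25 to 30. A patient vaccinated 18 months before enrollment has 6 protected months and 24 unprotected ones. If both remain labelled recently vaccinated, the recent group's rate drifts toward the older group's rate and the contrast shrinks.

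Two things are at stake. A null result from an enrollment-group comparison could be read, against a stated power of 0.81, as evidence that recent vaccination makes no difference. And the study's question is how long protection lasts, which is the feature that a fixed label blurs.

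**Working it through.** **Inputs from the article.** 792 patients at 1:5, so 132 older and 660 recent; 29.0 per 100 py unprotected; 20.88 per 100 py protected (0.72 × 29.0); 2.5 years; α = .05, taken as two-sided because that reproduces the stated power.

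**Assumptions.** No attrition and no revaccination in the base case. Time since vaccination at enrollment within the recent group is not given, so it is varied.

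**Formula.** Wald test of the log rate ratio with Poisson counts: power = Φ(|ln RR| / √(1/E₀ + 1/E₁) − 1.96), where E₀ and E₁ are the expected events.

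**Step 1: reproduce 0.81.** E₀ = 132 × 2.5 × 0.29 = 95.7. E₁ = 660 × 2.5 × 0.2088 = 344.5. |ln 0.72| = 0.3285; standard error = √(1/95.7 + 1/344.5) = 0.1156; ratio 2.843; power = Φ(0.883) = 0.811. The stated figure is right for a relative risk of 0.72 throughout.

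**Step 2: apply the 2-year window, groups fixed at enrollment.** With p the mean number of protected years per recent patient, the recent rate is [p × 0.2088 + (2.5 − p) × 0.29] / 2.5.

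| Time since vaccination at enrollment | p | Recent rate /100 py | RR | E₁ | Power |
|---|---|---|---|---|---|
| All zero (best case) | 2.0 | 22.50 | 0.776 | 371.3 | 0.60 |
| Even over 0–1 year, or half new and half even over 0–2 | 1.5 | 24.13 | 0.832 | 398.1 | 0.37 |
| Even over 0–2 years | 1.0 | 25.75 | 0.888 | 424.9 | 0.18 |

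Best case in full: |ln 0.776| = 0.2536; standard error = √(1/95.7 + 1/371.3) = 0.1146; ratio 2.212; Φ(0.252) = 0.60. Poisson simulation gives 0.79 undiluted, 0.59 in the best case and 0.19 for the even 0–2 spread.

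**Step 3: sensitivity.** A one-sided test raises the best case only to 0.72. Assumed attrition of 10% to 20% per year lowers it to 0.57 to 0.54. At 1:5 and 2.5 years, a power of 0.80 for fixed groups would need about 1,270 patients (RR 0.776) to about 5,650 (RR 0.888).

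**Step 4: person-time split at 2 years since vaccination.** The contrast stays at 0.72. E(unprotected) = 0.29 × [330 + 660 × (2.5 − p)], where 330 = 132 × 2.5; E(protected) = 0.2088 × 660 × p.

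| p | E unprotected | E protected | Power |
|---|---|---|---|
| 2.0 | 191.4 | 275.6 | 0.94 |
| 1.5 | 287.1 | 206.7 | 0.95 |
| 1.0 | 382.8 | 137.8 | 0.91 |

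These figures make no allowance for calendar-time adjustment and are optimistic to that extent.

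**The case against.** The strongest reply is that no sentence says group membership stays fixed during follow-up. In a Cox model the exposure is itself a covariate, and time since vaccination is an obvious time-varying one. The detail may sit in the full protocol or analysis plan, which are not shown. This stands: a fixed label is inferred from how the groups are defined and counted. But it does not rescue 0.81, because a time-updated analysis would have a different power (Step 4). The clause is also conditional, and the raw rates come with no rule for moving person-time.

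A second reply is that the step at 2 years is a planning simplification. That is fair, and it is why a reader should not conclude that proportional hazards must fail in the real data. Yet the same idea is the hypothesis in *Scientific Rationale* and the basis of the cut-off. If protection in fact outlasts 2 years, some of the older group is not at the baseline rate, and 0.72 is then too strong for a different reason.

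Third, *Study Procedure* expects a higher rate in an underprotected population, which would raise power. To bring the best case from 0.60 back to 0.81, events in both groups would have to rise by (2.843 / 2.212)² = 1.65, that is, to about 48 per 100 py at baseline. The article gives no such figure.

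Fourth, a reader might infer that a true effect would probably be missed. The documents do not support that. The best case of 0.60 makes detection more likely than not, and the article's talk of newly vaccinated patients, with titers drawn 4 weeks after vaccination, fits a group weighted toward recent doses. The 0.18 needs an even 0–2 year spread that nothing in the article establishes.

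Fifth, a reader might infer that revaccinated patients remain in the older group, or that the study cannot address duration at all. The article says neither. Revaccination is possible but not quantified, and the titer analyses over time bear on duration.

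**Conclusion.** The point holds as an internal contradiction with a wrong stated figure. The 0.81 needs a relative risk of 0.72 for all 2.5 years in every recent patient, while the plan assumes that protection ends at 2 years. For groups kept as classified at enrollment, with complete follow-up and no revaccination, the relative risk is at best 0.776 with power about 0.60. It is 0.888 with power about 0.18 under an even 0–2 year spread. The direction does not depend on the unreported distribution, since even a patient vaccinated at enrollment passes 2 years before follow-up ends; only the size does.

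It would go too far to say flatly that the study is underpowered. That depends on whether exposure is updated, which the article leaves open, and updating would give about 0.91 to 0.95 before calendar-time adjustment. What can be said firmly is that 0.81 matches neither analysis.

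**What to change.** 1. State that the primary Cox model and the raw rates use time since last documented vaccination (<2 versus ≥2 years) as a time-updated exposure. Split each patient's person-time at 2 years, and reset at revaccination where the date is captured.
2. Adjust for or stratify by calendar period. Crossover places ≥2-year time later in follow-up, and *Limitations* reports that the study ran during the pandemic, with a new cause of pneumonia. Without this, the split could create a spurious excess in the ≥2-year category.
3. Report the enrollment-group comparison alongside, since it is less exposed to that confounding.
4. Reconcile *Study Procedure* with the amendment and restate the power for the primary analysis: at most about 0.60 for fixed groups, or about 0.91 to 0.95 before calendar-time adjustment for time-updated exposure.

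**Cost.** Mostly wording and programming; baseline vaccination status is documented and vaccination timing is already an analysis variable. Capture of revaccination dates during follow-up must be confirmed, because the registry alerts listed in *Data Collection* do not mention vaccination. Follow-up is complete and analysis is under way, so the sample cannot change. The choice of primary exposure should be recorded before outcomes are compared by group, or declared post hoc if that has already happened.

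### The stated power of 0.81 applies the 0.72 relative risk for 2.5 years, although the plan's own assumption ends protection 2 years after vaccination

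*Protocol article*

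**What the plan says.** In the protocol article, Study Procedure gives the effect assumption: "we assume protection from pneumonia in the first 2 years to be equal to the protection recently demonstrated in an adult immunocompetent target population". The value taken from that population is 0.72, and once the 2 years are over the rate is assumed to go back to its baseline level. The expected rates are 29.0 and 20.88 per 100 patient-years. The same section words the comparison as newly vaccinated patients "compared to patients vaccinated more than 2 years before enrollment".

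Amendment After Interim Study Report counts the groups at enrollment: "596 had been vaccinated less than 2 years ago, and 114 had been vaccinated 2 or more years before enrollment". It adds "This represents a ratio of 1:5", keeps 0.72, and concludes that "792 patients were then considered sufficient if the observation period was extended to 2.5 years", with power 0.81 at alpha .05. Study Design confirms the longer follow-up: "During months 25-30, only the primary end point will be recorded".

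Study Conduct and Statistical Analyses says that raw event numbers and "raw rates of events per 100 patient years will be computed" for the comparison of the two groups. It adds a Cox model that may include time-varying covariates where applicable. It does not name time since vaccination as one of them.

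**The concern.** The two assumptions cannot both hold over 2.5 years. If protection ends 2 years after the dose, a patient vaccinated on the day of enrollment has 2.0 protected and 0.5 unprotected years. A patient enrolled 18 months after the dose has 0.5 protected and 2.0 unprotected years. If both stay in the recent stratum throughout, unprotected time is counted as recently vaccinated time.

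Three things follow for a comparison of enrollment strata:

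- The rate ratio is diluted toward 1, by an amount that depends on how long after the dose patients happened to enroll.
- The added months 25 to 30 contain no protected time for patients dosed at or before enrollment and not revaccinated, so the extension can lower power.
- A non-significant result could be misread as evidence against waning on a question meant to inform revaccination guidance.

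**Working it through.** **Inputs.** From the amendment: 792 patients, 1:5, 2.5 years, relative risk 0.72, alpha .05. The ratio gives 132 older and 660 recent patients. From Study Procedure: 29.0 and 20.88 per 100 patient-years, with protection ending at 2 years. Sidedness is not stated; two-sided is used because it fits both published figures. A two-sided comparison of proportions 0.29 and 0.2088 gives 445 per group against the stated 442, while the one-sided version gives 351.

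**Formula.** Wald test of the log rate ratio with Poisson events:

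power = Φ(|ln RR| / √(1/E_old + 1/E_recent) − 1.96)

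**Step 1: reproduce 0.81, with 0.72 held for 2.5 years.**

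- E_old = 132 × 2.5 × 0.29 = 95.7
- E_recent = 660 × 2.5 × 0.2088 = 344.5
- SE = √(1/95.7 + 1/344.5) = 0.1156 and |ln 0.72| = 0.3285
- Power = Φ(0.3285/0.1156 − 1.96) = **0.811**

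The exact interim ratio (about 127:665) gives 0.801.

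**Step 2: apply the plan's 2-year step to fixed enrollment strata.** A patient enrolled t0 years after the dose has 2 − t0 protected years. The stratum's average rate ratio is 1 − 0.28 × (protected share of 2.5 years). The distribution of t0 is not given, so the cases below are assumptions.

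| Assumed time since dose at enrollment | Mean protected years | RR | E_recent | Power |
|---|---|---|---|---|
| (a) all on enrollment day | 2.0 (80%) | 0.776 | 371.3 | **0.60** |
| (b) half day 0, half uniform 0–2 years | 1.5 (60%) | 0.832 | 398.1 | **0.37** |
| (c) uniform 0–2 years | 1.0 (40%) | 0.888 | 424.9 | **0.18** |

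For (a): SE = √(1/95.7 + 1/371.3) = 0.1146, |ln 0.776| = 0.2536, power = Φ(2.212 − 1.96) = 0.60.

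**Step 3: effect of the extension on fixed strata.** Stopping at 2.0 years gives 0.72 in case (a) and 0.22 in case (c). Going on to 2.5 years lowers these to 0.60 and 0.18.

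**Step 4: split person-time at the second anniversary of the dose.** The older stratum contributes 132 × 2.5 = 330 patient-years, all at 2 years or more. The recent stratum contributes 660 × 2.5 = 1650, divided by current time since dose.

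| Case | <2 years, patient-years | ≥2 years, patient-years | Share of ≥2 years from recent stratum | Power |
|---|---|---|---|---|
| (a) | 1320 | 330 + 330 = 660 | 330/660 = 50% | 0.94 |
| (b) | 990 | 330 + 660 = 990 | 660/990 = 67% | 0.95 |
| (c) | 660 | 330 + 990 = 1320 | 990/1320 = 75% | 0.91 |

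These figures precede calendar adjustment, attrition and overdispersion. Adding half-year calendar terms, with enrollment assumed uniform over 1.5 to 2.5 years, gives about 0.83 to 0.92.

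**Sensitivity of fixed strata.** Assumed attrition of 10–20% per year gives 0.57–0.54 in case (a) and about 0.18 in case (c). An assumed rate of 40 per 100 patient-years in the older stratum gives 0.74 and 0.23, against 0.92 undiluted.

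**The case against.** The strongest reply is that the article nowhere says that group membership is frozen during follow-up. Parts of it describe the groups simply by time since vaccination. The Cox model may use time-varying covariates, and time since the last dose is an obvious candidate. A condensed article may leave the allocation of person-time to the full protocol or SAP. This stands, so one cannot say that the planned analysis misclassifies person-time, only that the article does not commit to avoiding it. It does not rescue the power figure: split person-time gives 0.91 to 0.95 before adjustment, and the 0.81 needs 0.72 throughout the recent stratum.

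Several stronger readings are tempting but unsupported:

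- **That 0.60 is a ceiling on the study's power.** It is the best case only for fixed strata, a two-sided test and 29.0 per 100 patient-years. Study Procedure itself expects a higher rate in underprotected patients. The one-sided Schoenfeld route gives 0.822 as planned and 0.655 in case (a).
- **That power is 0.18.** This rests on an assumed uniform spread. The article calls the group newly vaccinated and sets its baseline titer 4 weeks after the dose, which suggests that some patients enrolled soon after vaccination.
- **That every recent patient crosses the 2-year point.** This holds for those who complete 30 months without a new dose. Death, transfer, withdrawal and routine revaccination are all possible.
- **That a null result is likely even if the hypothesis is true.** In case (a) significance is more likely than not. Null is the likelier outcome only with fixed strata and cases such as (b) or (c).

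**Conclusion.** The contradiction is in the text and affects the headline power. The published 0.81 depends on 2.5 years of protection, which the plan's own effect assumption excludes. Under that assumption, at 29.0 per 100 patient-years, two-sided alpha .05 and full follow-up, a comparison of fixed enrollment strata has power of 0.60 at best. Across the assumed distributions of time since dose the range is about 0.2 to 0.6. A split-person-time analysis would have more than 0.81 before calendar adjustment, attrition and overdispersion, and less after them. Whether the primary rate ratio will actually be diluted depends on a choice that the article leaves open. Follow-up is complete, so restating power cannot change the sample, but the choice of exposure definition still determines what the primary result means.

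**What to change.** In the primary rate table and the Cox model, define exposure as current time since the last pneumococcal dose. Each patient contributes person-time and events to the <2 years category until the second anniversary of that dose, and to the ≥2 years category afterward. Use a patient-level robust variance and a calendar-period term. Keep the comparison by enrollment stratum as a sensitivity analysis.

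In the amendment, replace 0.81 with the power of the analysis actually used, computed from the observed distribution of time since dose at enrollment. Pending that, the figures are about 0.2 to 0.6 for fixed strata, or about 0.91 to 0.95 for split person-time, with a note that the latter falls after calendar adjustment, attrition and overdispersion.

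The change needs no new patients or visits: vaccination history is already collected, so the cost is a data split and analysis wording. The price is inferential. In the scenarios above, 50–75% of the ≥2 years person-time comes from patients who began in the recent stratum. The contrast is then largely before versus after within patients and relies on adequate calendar-time adjustment, including for the pandemic that the Limitations section describes.
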